### Statistical treatment

Due to the pilot nature of this study, descriptive statistics will be used to summarize feasibility outcomes, including recruitment, adherence, and retention rates. Variability in biomechanical measures will be estimated using means, standard deviations, and confidence intervals to guide sample size calculations for a future RCT. Given the small sample size, formal hypothesis testing will not be conducted. Preliminary pre-post comparisons of biomechanical outcomes will be reported using effect sizes (e.g., Cohen's d) and confidence intervals. Statistical analyzes will be performed with IBM SPSS Statistics version 28.0 (IBM Co., Armonk, NY, USA).

An external biostatistician will be contracted to perform all statistical treatments and control for any potential observer bias. The biostatistician will also manage the dataset to adjust for any missing data. We envision the use of multiple imputation where necessary, with assumption that the mechanism of missing data points was missed at random.

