**Methods:**

Ten children will participate in this single-arm waitlist-controlled pre-post feasibility trial. Children 4–6 years old with spastic diplegia cerebral palsy (Gross Motor Function Classification System level III) will engage in the intervention with individually adapted stand-on PMD use for three months at home, neighborhood, and family places. Biomechanical assessment will take place at baseline (3 months prior to intervention), at pre-, and at post-intervention. Exploratory outcome measures include center of pressure variables, kinematic variables of full-body coordination, and lower extremity muscle co-contraction during gait, sit-to-stand, and balance tasks.

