## Methods

### Study design

This design of the presented study protocol adheres to the established definition of a pilot/feasibility study, as outlined by the CONSORT extension for pilot and feasibility studies. Additionally, given the pilot nature of this project (R03) and the population (4–6-year-old children) who can undergo spurs of physical maturation, we selected a waitlist control design in which a baseline evaluation is administered 3 months prior to the pre-intervention evaluation. This is performed to control for changes in the secondary outcome measures that are due to maturation and not the proposed intervention.

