### Participants

Study inclusion criteria {10} include: 1) Diagnosis of spastic diplegia cerebral palsy, GMFCS level III (28); 2) between 4 and 6 years old (age band selected based on the benefits of early intervention (12, 24) and the age-limitation imposed from the size constraints of the PMDs (toy cars) selected for the intervention); 3) able to stand and to walk short distances (at least 10 meters) with or without external assistance; 4) physician medical clearance to participate; and 5) exhibit sufficient cooperation and attention so that simple verbal instructions can be followed. Potential participants will be excluded if they: 1) have notable orthopedic conditions (e.g., lower extremity amputation; recent hip surgeries or soft tissue lengthening); 2) inadequate vision to complete study's procedures safely; 3) serious/unstable cardiac conditions that prevent engagement in the Evaluation Sessions; and 4) any other factor that might hinder full participation in the study or confound interpretation of the results. Although we will aim to recruit children who are not receiving balance/walking-specific rehabilitation, children can be engaged in therapy sessions while taking part in the study. We will account for the type and amount of rehabilitation statistically to maintain rigor of research and to generate robust homogeneous findings to support the subsequent study.

Ten children will be recruited {15} from local rehabilitation programs. Although no sex-difference in balance performance has been reported for children with cerebral palsy at the age band of interest (29), smaller differences in trunk control have been reported for children with cerebral palsy ages 8–14 years (30) and typically developing children (31, 32). Thus, we will aim to recruit five boys and five girls since sex will be considered as a biological factor (33–35) in the statistical analyses of the subsequent larger grant application.

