### Assessment protocols

Biomechanical assessments will be performed at three timepoints (Figure 1): baseline (3 months prior to intervention), pre-intervention (same day as child receives the individually adapted PMD), and post-intervention (3 months after receiving the individually adapted PMD). Reflective markers will be placed on anatomical landmarks according to a modified Plug-in-Gait model for full-body kinematic tracking. Surface EMG electrodes will be placed bilaterally on tibialis anterior, medial gastrocnemius, rectus femoris, biceps femoris, and gluteus maximus, following SENIAM guidelines.

The following standardized protocols will be administered:

***Static Balance***: NIH Toolbox Standing Balance Test (42). Participants will stand barefoot on a single force platform in a standardized stance (feet hip-width apart, arms at sides) for up to 50 s with eyes open, followed by 50 s with eyes closed. Three trials will be collected for each condition, with rest periods between trials as needed. These two conditions will also be performed with children standing on an unstable surface (Airex®). Tandem stance will also be attempted per protocol.

***Dynamic Balance***: Five-Times-Sit-to-Stand Test (5TSTS) (43) and Modified Timed Up and Go (mTUG) (44). For the FTSTS, participants will be seated on a height-adjustable bench (allowing for 90° of hip and knee flexion) with feet resting on the force plate. Participants will be instructed to stand up and sit down five times as quickly as possible with arms crossed over the chest. Three trials will be collected with rest periods as needed. Hand support will be provided for those who cannot independently rise from the bench. For the mTUG, participants will rise from the seated position, walk 3 meters at a self-selected pace, turn 180°, return to the chair, and sit down. The turning period of the task will be captured on the force plate. Three trials will be collected with adequate rest between trials. Hand-held support will also be provided for those who are unable to walk independently.

***Gait***: 10-Meter Walk Test (45). Participants will walk along the instrumented walkway at self-selected comfortable speed and at fast pace. Three trials will be collected for each speed condition, with rest periods as needed. Hand-held support will be provided for those who are unable to walk independently.

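### The baseline visit is there to control for maturation, but the only change analysis the article names, pre versus post, does not use it

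*Protocol article*

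**What the plan says.** The abstract describes one group: "Ten children will participate in this single-arm waitlist-controlled pre-post feasibility trial". With no concurrent control, each child's own wait is the only comparator. Study design states the arrangement, "we selected a waitlist control design in which a baseline evaluation is administered 3 months prior to the pre-intervention evaluation", and its purpose: "This is performed to control for changes in the secondary outcome measures that are due to maturation and not the proposed intervention". The reason given is "the population (4–6-year-old children) who can undergo spurs of physical maturation".

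Assessment protocols keeps three separate time points: "baseline (3 months prior to intervention), pre-intervention (same day as child receives the individually adapted PMD), and post-intervention (3 months after receiving" the device. The wait and the intervention period are therefore equally long, 3 months each.

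On the analysis of change, Statistical treatment says: "Preliminary pre-post comparisons of biomechanical outcomes will be reported using effect sizes", with Cohen's d as the example, and with confidence intervals. The same section plans means, standard deviations and confidence intervals for the biomechanical measures, to describe variability, and rules out formal hypothesis tests. It mentions neither the baseline visit nor the change from baseline to pre-intervention. The secondary objective says the described changes are to inform outcome selection and sample-size estimation for future trials.

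**The concern.** A baseline visit controls for maturation only if some estimate uses it. The article gives the visit that purpose and then names a comparison that omits it, so the stated design and the stated analysis do not meet. Read literally, each pre-post effect size adds together whatever the device does and whatever three months of growth do.

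Two later decisions are exposed. Outcomes that mature fastest would look most responsive to the device and could be chosen for that reason. And if a pre-post change is carried into the planning of the randomised trial, that trial could be too small, because maturation occurs in both of its arms and does not contribute to the difference between them.

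**Working it through.** There is no power, alpha, effect size or standard deviation behind the ten children, so there is no figure of the plan's own to reproduce. The check sets out what each comparison estimates and then shows illustrative sizes.

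**What each comparison estimates.** Let m be the maturation per 3 months, equal in both periods, and e the device effect.

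- Expected (post − pre) = m + e.
- Expected (post − pre) − (pre − baseline) = (m + e) − m = e.

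A simulation with n = 10, correlation 0.8 between visits and m = 0.3 SD agrees: for e = 0 the means are 0.30 and 0.00, and for e = 0.5 they are 0.80 and 0.50. If maturation differs between the periods (m1 in the wait, m2 in the intervention), the second line becomes e + (m2 − m1). A practice gain that is larger between the first two visits than between the last two enters in the same way.

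**Shift in a pre-post effect size when e = 0.** The article gives neither m nor the correlation r between visits, so both are assumptions, and it does not fix the standardiser of Cohen's d. With the between-child SD the shift is m itself. With the SD of change it is m / √(2(1 − r)); for example, 0.2 / √(2 × 0.2) = 0.32 at r = 0.8.

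| m (SD per 3 months, assumed) | between-child SD | SD of change, r = 0.7 | r = 0.8 | r = 0.9 |
|---|---|---|---|---|
| 0 | 0 | 0 | 0 | 0 |
| 0.2 | 0.20 | 0.26 | 0.32 | 0.45 |
| 0.3 | 0.30 | 0.39 | 0.47 | 0.67 |

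**Illustration for the later trial.** Suppose the observed pre-post change is 0.8 between-child SD and is taken as the difference between two arms (two-sided 0.05, 80% power). By the normal approximation, n per arm = 2(1.96 + 0.84)² / 0.8², which rounds up to 25. The net effect is 0.8 − m.

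| m (assumed) | net effect | n per arm needed | power with 25 per arm |
|---|---|---|---|
| 0 | 0.8 | 25 | 81% |
| 0.1 | 0.7 | 33 | 70% |
| 0.2 | 0.6 | 44 | 56% |
| 0.3 | 0.5 | 63 | 42% |
| 0.4 | 0.4 | 99 | 29% |

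**Price of the within-child difference.** Let s be the between-child SD.

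- Variance of post − pre: 2s²(1 − r).
- Variance of post − 2·pre + baseline with equal correlations: 6s²(1 − r). The SD ratio is √3 = 1.73.
- With AR(1) correlation the ratio is √(3 − r): 1.52, 1.48 and 1.45 at r = 0.7, 0.8 and 0.9.

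With ten children and equal correlations, the 95% CI half-width (t, 9 df) goes from 0.45 to 0.78 SD at r = 0.8, and from 0.32 to 0.55 SD at r = 0.9. With eight children (the 80% retention criterion) and r = 0.8 it goes from 0.53 to 0.92 SD.

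**Bias against noise.** With n = 10 and equal correlations, root-mean-square error is √(m² + 2(1 − r)/10) for pre-post change and √(6(1 − r)/10) for the difference.

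| m (assumed) | r | pre-post | difference |
|---|---|---|---|
| 0.2 | 0.7 | 0.32 | 0.42 |
| 0.2 | 0.8 | 0.28 | 0.35 |
| 0.2 | 0.9 | 0.24 | 0.24 |
| 0.3 | 0.8 | 0.36 | 0.35 |
| 0.3 | 0.9 | 0.33 | 0.24 |

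Neither estimate is better throughout, so the two should be shown together.

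**The case against.** The strongest reply is that silence is not exclusion. Statistical treatment does not say that only pre-post comparisons will be made. The title and abstract use pre-post as a name for the whole three-visit design, the planned means and SDs are not limited to two visits, and an analysis plan not shown could contain the wait-period contrast. This stands against the stronger reading that maturation is bound to remain in every reported result. The text does not support that. What it supports is narrower: the one comparison it names does not serve the purpose it gives the baseline visit.

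A second reply is that little hangs on it. The primary objective is feasibility, efficacy is expressly not tested, and the Discussion calls the findings exploratory. Statistical treatment ties variability, not Cohen's d, to the sample-size calculation, and no decision rule uses the pre-post effect size. All three visits are scheduled and the biomechanical data are to be shared, so the contrast could still be computed later. This largely stands and limits the severity. It does not remove the point, because the secondary objective ties the described changes to outcome selection and sample-size estimation.

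Third, the within-child difference is noisy at n = 10 and rests on equal maturation in both periods. Growth spurts, which the article itself raises, need not cancel. This stands against making the difference the sole or lead estimate. Pre-post change read alone as the device effect, however, assumes no maturation at all, which Study design does not accept.

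A reader might also infer from Participants, "We will account for the type and amount of rehabilitation statistically to maintain rigor of research", that a second promise is broken because ten children cannot support covariate adjustment. The documents do not establish this. Statistical treatment does not withdraw the promise, and one covariate with ten children is imprecise but estimable (10 − 2 = 8 residual degrees of freedom). It is a side issue here.

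**Conclusion.** The point holds in a limited form. Study design gives the baseline visit the task of controlling for maturation, and the only change analysis named does not use that visit. Followed as written, the pre-post effect sizes include any 3-month maturation and can mislead outcome selection and the planning of the later trial.

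The size cannot be stated, because the article gives no maturation rate, correlation or standardiser. It is zero if maturation is zero; the other figures above illustrate assumed values of 0.1 to 0.4 SD per 3 months. The within-child difference removes maturation only if it is similar in both periods and there is no fading practice effect.

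This should be fixed, but it is not a critical fault. The criteria on recruitment, retention and adherence are untouched, and the fourth criterion concerns standard deviations, which a common shift in the mean does not alter.

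**What to change.** In Statistical treatment, state that for every biomechanical outcome:

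- the baseline-to-pre and pre-to-post changes will be reported side by side, each with a 95% CI;
- the within-child difference (post − pre) − (pre − baseline) will be reported with its 95% CI;
- the pre-post effect size alone will not be read as the effect of the device.

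Add that the difference assumes similar maturation in both periods and no fading practice effect, and that its SD is about 1.5 to 1.7 times that of the pre-post change. Any illustration of the bias should be marked as an assumption and should include zero.

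The cost is a few sentences and some extra analysis; no visit or measurement is added. The drawback is wide intervals for the difference with ten children, which the side-by-side display makes visible.

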#### Secondary (exploratory) objective

To descriptively characterize changes in biomechanical measures related to static balance, dynamic balance, and gait following three months of adapted stand-on PMD use, with the purpose of informing outcome selection and sample-size estimation for future trials.

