### Intake screening and consent/assent procedures

Once potential participants contact us, the initial intake screening to confirm eligibility will be performed by the research team's physical therapist who has 30 + years of experience with evaluating and treating children with neurologic condition, including cerebral palsy. This intake, which takes place at the Laboratory of Applied Biomechanics and Engineering at the University of North Florida, involves assessment of each participants’ anthropometric measurements, range of motion, and muscle tone. Weight (kg) will be measured using a calibrated digital scale (Pelstar Professional Scale, model 349KLX, China) with participants standing independently when possible, or seated when standing is not feasible. Height (cm) will be measured using a wall-mounted stadiometer (Seca, model 264, Germany) with clinician assisting child to maintain a stand-up posture when needed. Following, with the child lying supine on a floor mat, lower-extremity and bilateral foot length (cm) will be measured using a tape measure; width (mm) of bilateral knees, ankles, and forefeet will be measured using a digital caliper. Passive range of motion will be assessed using a standard goniometer to measure joint angles accurately. Muscle tone will be assessed using the modified Ashworth Scale, which provides a reliable grading of spasticity levels in each of the joints of the participants’ extremities.

Once confirmed eligibility, parents and children will meet with the PI of the study ([name]) at a dedicated private room for the informed consent/assent procedures approved by the University's Institutional Review Board (UNF IRB LEG-2147539). A basic set of medical information will be reviewed to confirm participant's eligibility for the study and physician clearance for participation in the activities associated with the research study will be obtained. If a participant withdraws, we will document the reason for withdrawal and recruit a new participant to replace the individual who withdrew.

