### Assessment procedures and outcome measures

The primary aim of this study is to determine whether a full-scale RCT is feasible. The feasibility of a future RCT will be determined using the following progression criteria:
-Recruitment Feasibility: At least 70% of eligible participants consent to enroll within the recruitment period.-Retention Rate: At least 80% of participants complete all study visits and assessments.-Adherence: Participants use the stand-on PMD for an average of at least 20 min per day based on device tracking.-Variability of Primary Outcomes: Standard deviation of biomechanical outcomes should allow for a sample size estimation in a full-scale trial.

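### Cohen's d from ten children runs about 4 to 9% too high on average unless corrected; report Hedges' g with the raw quantities behind it

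*Protocol article*

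**What the plan says.** The Abstract (Methods) gives the design and size: "Ten children will participate in this single-arm waitlist-controlled pre-post feasibility trial". A child who withdraws is replaced (Intake screening and consent/assent procedures: "recruit a new participant to replace the individual who withdrew"), so ten pairs is the base case.

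Statistical treatment has two relevant sentences. One covers reporting: pre-post comparisons, described as preliminary, are to be given as "effect sizes (e.g., Cohen's d) and confidence intervals". The other covers planning: "Variability in biomechanical measures will be estimated using means, standard deviations, and confidence intervals to guide sample size calculations for a future RCT". The same section rules out inference: "Given the small sample size, formal hypothesis testing will not be conducted".

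Two other places bear on how the results will be used. The secondary objective describes the biomechanical changes "with the purpose of informing outcome selection and sample-size estimation for future trials". The progression criterion on variability (Assessment procedures and outcome measures) reads "Standard deviation of biomechanical outcomes should allow for a sample size estimation in a full-scale trial".

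Cohen's d is the only effect size named, and it is named as an example. The article states neither a small-sample correction nor which SD divides the mean change.

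**The concern.** Cohen's d divides a mean by an estimated SD. In small samples the reciprocal of the SD is too large on average, so d overstates the standardised effect. The error runs in one direction, its size is known, and one multiplication removes it.

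It deserves a line here because the pilot exists to feed later planning. Required sample size varies as 1/d², so a proportional error in d roughly doubles when carried into a sample size. For paired data, d also has several possible denominators. They give different values and different amounts of bias, so a reader who wants to apply the correction must know which was used.

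**Working it through.** The article states no effect size, alpha, power or derived sample size, so there is no figure of its own to reproduce.

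**Inputs.** n = 10 pairs (Abstract, Methods), hence m = n - 1 = 9 degrees of freedom for the SD of change or the pre-intervention SD. Normality is assumed, with equal SDs at the two visits. The pre-post correlation r is not given and is varied from 0 to 0.9.

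**Bias factor, 9-df SD.** J(m) = Γ(m/2) / [√(m/2) · Γ((m-1)/2)].
- J(9) = Γ(4.5) / [√4.5 · Γ(4)] = 0.914.
- Mean inflation of d: 1/0.9139 = 1.094, or 9.4%.
- Simulation (400,000 replicates, n = 10, true raw d = 0.5) gives ratios of 1.093 to 1.097 for both the SD of change and the pre-intervention SD.
- With only 8 completers (the 80% retention criterion, no replacement), 1/J(7) = 1.126, or 12.6%.

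**Bias with a pooled pre/post SD** (same simulation): 4.3% at r = 0, 5.7% at r = 0.5, 8.1% at r = 0.9.

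**Effect on a sample size, if d were used for one.** N is proportional to 1/d².
- 9-df SD: J² = 0.835, so N is about 16% short; 1/0.835 - 1 is about 20% more needed.
- Pooled SD: 1/1.043² = 0.919 (about 8% short) at r = 0, and 1/1.081² = 0.856 (about 14% short) at r = 0.9.

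**Sampling error for comparison.**
- Observed d = 0.5 on the SD of change, n = 10: the noncentral-t 95% CI is -0.17 to 1.15, a half-width of (1.15 + 0.17)/2 = 0.66. The bias at a true d of 0.5 is 0.5 × 0.094 = 0.047.
- An SD on 9 df has a 95% CI from 0.69 to 1.83 times its estimate.

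**Does the choice of SD push in one direction?** With equal SDs, d on the SD of change equals raw d / √[2(1-r)]. Assume two-sided 5%, 80% power, 1:1 allocation and a true raw d of 0.5, so that a comparison of post scores needs 63 per arm. Sizing that comparison from d on the SD of change, with its 9.4% inflation, gives:

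| r | per arm |
|---|---|
| 0 | 105 |
| 0.3 | 74 |
| 0.5 | 53 |
| 0.7 | 32 |
| 0.8 | 21 |

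The break-even is 2(1-r) = 1/J² = 1.197, so r = 0.40. Below it the trial is too large, above it too small. If the later trial analyses change scores, d on the SD of change is the matching scale and only the 9.4% remains.

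**The case against.** The strongest reply is that the article does not plan to size a trial from d. The planning sentence names means, SDs and confidence intervals, and the progression criterion rests on the SD. Cohen's d sits in a separate reporting sentence, as an example that Hedges' g would also satisfy. The correction and the denominator are details an article may leave to its analysis plan. The bias is a small fraction of the confidence interval, which the article already promises, and the Discussion calls the findings exploratory. De-identified participant-level data will be deposited, so anyone could compute g later.

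Most of this stands. It limits the point to an improvement of a named method; it does not show an error. What remains is that d is the only effect size named, and that the secondary objective ties the changes it will summarise to sample size and outcome selection. Wide intervals do not justify keeping a known bias that costs nothing to remove.

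A reader might infer that the next trial would be too small. The documents do not support that. Only the secondary objective links the changes to sizing, and it does not mention d. No section carries a single-arm pre-post d over to a between-group effect. The unnamed denominator can oversize as well as undersize a trial. Nor does the text say that d will be left uncorrected, or that different outcomes will be scaled differently.

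**Conclusion.** The point holds as a minor, free improvement. At n = 10 an uncorrected d is inflated on average by about 9% on a 9-df SD, or by about 4 to 8% on a pooled pre/post SD. If it were used for sizing, the bias alone would understate N by up to about 16%. That consequence is conditional, since the article mainly points to means, SDs and confidence intervals for this purpose, and sampling error is much larger than the bias.

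The figures assume normal data, equal SDs at both visits and ten complete pairs. The correlations, alpha, power and true effect used above are illustrative, because the document gives none.

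**What to change.** In Statistical treatment, amend the sentence on pre-post comparisons to:
- report Hedges' g in place of Cohen's d (0.914 × d at n = 10 for a 9-df SD, with the factor recomputed for the number of pairs actually available), with a noncentral-t confidence interval. That interval is exact under normality for the SD of change and approximate for the other denominators;
- name one standardiser and use it for all outcomes;
- tabulate alongside it the raw mean change, SD of change, pre-intervention SD and between-visit correlation;
- state that a future trial will be sized from these raw quantities, on the scale it will analyse, and not from the pilot effect size.

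The cost is one multiplication and a few table columns. No extra data are needed. Reported effect sizes become slightly less favourable: an observed d of 0.5 becomes 0.914 × 0.5 = 0.457.

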Our proposed feasibility research is unique in that it looks at a quantitative measure of postural stability as children participate in independent self-directed functional activities with stand-on PMD within their natural environment. Additionally, the novel stand-on component derived from the built-in harness is unique and will allow for additional lower extremity loading. As children stand on the stationary surface (i.e., inside the PMD) that is self-directed through space (i.e., translation of the base of support), children must modulate lower extremity strength and proprioception to counteract external forces/perturbations and maintain balance. Preliminary evidence from a case study supports this expectation, showing significant improvement in dynamic balance control following 3 months of stand-on PMD use in a young child with spastic diplegic cerebral palsy (48). Thus, it is expected that our exploratory findings will lead to the future clinical trial testing the hypothesis that regular use of adapted PMD while standing and encountering natural environmental perturbations provides the practice and motor control learning needed to improve postural stability in children with impaired balance and mobility.

Considering the target population of young children with cerebral palsy (GMFCS level III), certain approaches for kinematic evaluations may not be feasible since many may exhibit disorders with processing of sensory information (49). This disorder may impact the placement of kinematic markers on the child's skin, which is a requirement to ensure exact quantification of joint amotions for traditional motion capture systems. Given this potential obstacle towards collecting data to address some of our secondary outcome variables, a multimodal toolbox (46) was developed to facilitate kinematic data collection and further calculations of whole-body coordination (e.g., trunk-pelvis vector coding). This open-source, Python-based platform enables motion capture and movement analysis by integrating signals from diverse sources, including retroreflective motion capture technologies, markerless video capture, inertial measurement units, among other sources, to enhance available biomechanical evaluations for pediatric populations with disabilities.

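### Multiple imputation under missing at random makes no exception for static-balance conditions that a child could not perform, where that assumption is doubtful

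*Protocol article*

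**What the plan says.** The study is small: "Ten children will participate in this single-arm waitlist-controlled pre-post feasibility trial". On missing data, Statistical treatment first sets the scope, "The biostatistician will also manage the dataset to adjust for any missing data", and then the method: "We envision the use of multiple imputation where necessary, with assumption that the mechanism of missing data points was missed at random". A value lost through equipment failure and a value absent because the child could not do the task are not distinguished.

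The same section gives the purpose of the estimates: "Variability in biomechanical measures will be estimated using means, standard deviations, and confidence intervals to guide sample size calculations for a future RCT". Variability is also one of the four progression criteria: "Standard deviation of biomechanical outcomes should allow for a sample size estimation in a full-scale trial".

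Two other places bear on why values might be missing. Under Participants, a child qualifies if "able to stand and to walk short distances (at least 10 meters) with or without external assistance". Under Assessment protocols, the static test asks for standing "for up to 50 s with eyes open, followed by 50 s with eyes closed", repeats both conditions on an unstable surface and adds an attempt at tandem stance. Hand support is provided for the sit-to-stand test (5TSTS), the modified Timed Up and Go (mTUG) and the walk test, but none is described for static balance. Table 1 labels the static COP variables as primary level.

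**The concern.** A child who needs help to stand may produce no COP value with eyes closed, on the unstable surface or in tandem, and the reason is the poor balance that the value would have measured. Missingness of that kind is not at random unless other recorded data explain it. Imputing under missing at random then draws a sway value from the children who managed the condition and assigns it to a child who did not.

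The pilot's means and SDs are meant to size the later randomised trial. An SD that is too small makes that trial too small, and a mean that looks too good misdescribes the population. With ten children, the imputation model can also carry only one or two predictors, so it has little means of repairing the problem.

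**Working it through.** **The plan's own figures.** The article states no missing rate, power or sample-size calculation, so there is nothing to reproduce. Everything below rests on stated assumptions.

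**Where missing at random is doubtful.**
- *Static balance (eyes closed, unstable surface, tandem):* assisted standers are eligible and no support is described. Inability is foreseeable and tied to the outcome.
- *5TSTS, mTUG, gait:* hand support is given, so inability need not produce a missing value.
- *Kinematics:* the Discussion warns that "certain approaches for kinematic evaluations may not be feasible since many may exhibit disorders with processing of sensory information". It attributes this to sensory processing, does not link it to the unseen joint angle, and offers markerless capture as a way round. These variables are secondary level.

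**Simulation inputs.** n = 10 (article). Assumed: a normal outcome with SD 1, higher being worse; one auxiliary predictor with correlation 0, 0.3, 0.6 or 0.8 to the outcome; proper normal-regression imputation with 20 imputations. The missing children are either those with the worst outcome (not at random) or those with the worst predictor (at random given the predictor). The average sample SD with full data is 0.97. A negative mean shift means that performance looks better than it is.

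| Situation | Average SD | Mean shift (true SDs) |
|---|---|---|
| Worst 1 missing, correlation 0.8, imputed | about 0.90 | about −0.08 |
| Worst 2–3 missing, imputed | 0.80–0.87 | −0.16 to −0.46 |
| Worst 2 missing, observed children only | about 0.76 | about −0.32 |
| Worst 3 missing, observed children only | about 0.70 | about −0.45 |
| 2 missing, truly at random, imputed | 1.03–1.14 | about 0 |

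Ranges run over the four correlations. Repeat runs move the entries by about 0.02.

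**Effect on a future sample size.** The required n is proportional to SD².
- SD ratios with two or three unable: 0.80/0.97 = 0.82 and 0.87/0.97 = 0.90, so the SD is about 10–18% low.
- n ratios: 0.82² ≈ 0.68 and 0.90² ≈ 0.80. The trial would have roughly two-thirds to four-fifths of the children it needs.
- One unable with a strong predictor: 0.90/0.97 = 0.93, so the SD is about 7% low.

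**Illustration** (assumed effect 0.5 true SD, two-sided 5%, 80% power). n per arm = 2(1.960 + 0.842)²/d².
- Correct SD: 15.70/0.25 = 62.8, so 63 per arm.
- SD 10% low: 62.8 × 0.81 = 50.9, so 51 per arm, with true power 71%.
- SD 20% low: 62.8 × 0.64 = 40.2, so 41 per arm, with true power 62%.

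**If missing at random holds.** The mean is unbiased, but with two missing the SD is inflated: 1.03/0.97 = 1.06 to 1.14/0.97 = 1.18, so about 6–18% high. With so few rows, imputation disturbs the SD in this case too, in the other direction.

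**Scale of sampling error.** The 95% interval for an SD from ten complete children is the estimate times √(9/χ²), which is 0.69 to 1.83 times the estimate.

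**The case against.** The wording is hedged: imputation is envisioned, and only where necessary. Nothing says that inability will be coded as missing and then imputed. The static test allows stands shorter than 50 s, and COP velocity is defined as path length over trial duration, so a short stand still yields a value. Inability on the harder conditions may be partly predictable from easier conditions, other visits or muscle tone. All of this stands. It limits the claim to what could happen in the unsupported static conditions.

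A reader might infer that missing at random is contradicted throughout. The article does not support that, given the hand support and the markerless route.

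A reader might also infer that imputation causes the bias, so that dropping it cures the problem. The table shows otherwise: the observed children alone give a smaller SD than imputation does, and a mean shift at least as large. A mixed model fitted to the observed data also assumes missing at random. The bias comes from who is missing.

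Nor does imputing outcomes conceal incompleteness as such, because completion of all visits and assessments is already a progression criterion. That overall count does not, however, show which conditions children could not do.

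Finally, the coding of inability may be set out in a full protocol or analysis plan that is not shown. The missing-at-random rule and its scope are stated in this article, though, and can be judged here.

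**Conclusion.** The concern holds in limited form. For unsupported static balance, a blanket missing-at-random rule is doubtful on the article's own eligibility and test conditions, and the COP variables affected are labelled primary level.

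The size depends on an unstated number of children. Two or three unable out of ten is an assumption. It gives an imputed SD about 10–18% low and a mean 0.16–0.46 SD too good under a normal outcome and one auxiliary predictor. With one child unable and a strong predictor, the bias is about 7–8% in the SD and 0.08 SD in the mean, which is minor beside the sampling error at n = 10.

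The case for change does not rest on size alone. A sway value imputed for a condition that the child could not perform describes nothing observable, whereas the inability itself is information that the pilot needs for choosing outcomes.

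**What to change.** Revise the missing-data statement as follows.

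1. Do not impute a value for a task that the child could not perform. Record 'attempted, unable' as its own result, separate from technical loss and refusal.
2. Score hold time from 0 to 50 s in every static condition, so that children who fail a condition still contribute data.
3. Report completion by task, condition and visit as a feasibility result.
4. Report observed-data means and SDs with the number of children behind each. State that they describe only children able to do the task and may understate the SD for the whole population when the later trial is sized.
5. Keep multiple imputation only as a labelled sensitivity analysis for technical losses. If it is extended to inability, include a not-at-random scenario.

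The cost is a change of wording and one recording field, settled before analysis. There are two downsides: some SDs will visibly rest on fewer than ten children, and the observed-data SDs still carry the selection bias, which this fix discloses without removing.
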